#### Sample Size and Power Calculation

The primary analysis is based on the intention-to-treat population of all children and adolescents with initial psychiatric diagnosis (addressed in hypothesis 4). In a first step, we calculated the number of children and adolescents to demonstrate the assumed effect in this population. Since the intervention takes place at family level, we determined the total number of children and adolescents and their families to be recruited in a second step.

We assume that 18 months after the baseline assessment 76% of children and adolescents in the intervention group and 90% in the control group still have a psychiatric diagnosis according to K-SADS-PL. Further, we suppose that 25/55/15/5% of the families have 1/2/3/4 children, so that on average a family has 2 children and adolescents. With a power of 80%, a two-sided alpha of 5% and an intracluster correlation of 0.05, we need 116 children and adolescents per group (232 children and adolescents in total) with an initial psychiatric diagnosis in 58 families per group (116 families in total) to detect this difference. We rounded up to 240 children and adolescents in 120 families. Additionally, we expect that 15% of children and adolescents show an initial psychiatric diagnosis according to K-SADS-PL. With this assumption, we have to recruit in total 800 families with 1,600 children and adolescents.

In this study, we have two additional populations. The first population consists of all children and adolescents (addressed in hypothesis 1) and the second population consists of all children and adolescents with initial mental health problems (addressed in hypothesis 2). For these two hypotheses, we calculated the power with which we can detect the assumed effects based on the sample size calculated for the primary analysis. This sample size enables us to demonstrate with a power of at least 80% the assumed between-groups difference of 0.25 standard deviations in the whole sample (continuous outcomes, hypothesis 1) 18 months after baseline assessment. Furthermore, for the population of hypothesis 2 we expect 400 children and adolescents in 200 families with initial mental health problems if the calculated sample size for the primary hypothesis will be included. In the population, we then can demonstrate a between-groups difference of 10% (80% of the children and adolescents in the intervention group still have mental health problems and 90% in the control group) with a power of 79%.

We used the modules “Tests for Two Proportions in a Cluster-Randomized Design” and “Tests for Two Means in a Cluster-Randomized Design” in PASS 15 (NCSS, LLC. Kaysville, Utah, USA) for these calculations.

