**Figure 1 F1:**
[figure not shown]
Overview of the CHIMPs study design.

If the family has been referred to the intervention group, the therapist who carries out the CHIMPs program is informed and the start of the intervention is initiated. If the family has been referred to the control group, no further treatment is provided within the CHIMPs study.

At 6 (T2), 12 (T3), and 18 (T4) months after baseline assessment, the families will be contacted again by the research staff. The questionnaires and diagnostic interviews for all three follow-up assessments are the same as at the baseline assessment. Families receive a financial compensation (up to €50) if a follow-up assessment is completed, in order to further promote a complete follow-up.

All study-related information will be stored securely at the study site. All records that contain names or other personal identifiers, such as locator forms and informed consent forms, will be stored separately from study records identified by code number. The coordinating study site will oversee the intra-study data sharing process.

All study outcomes, especially the primary outcome papers, will be published in peer-reviewed journals and presented at scientific conferences. All papers and abstracts must be approved by the coordinating site before submission.

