Data will be analyzed and reported according to the CONSORT statement. Mean and standard deviation will be presented for the continuous variables and absolute and relative frequencies for the categorical variables for the whole sample and separated by treatment groups. Since the relatives of a family are subject to common influences, cluster effects are generally to be expected. Therefore, the inferential statistics will be conducted using mixed models with the family and the relatives as random effects. As further covariates, recruitment center, treatment group, time, and the interaction between the two, as well as baseline variables that are unbalanced between the treatment groups. As further possible covariate, the type of clinic (university clinic vs. supply clinic) will be examined. For this purpose, baseline comparisons will be performed. If significant differences are found, this variable will be included in the model as a further fixed effect. We will use the direct Maximum-Likelihood as the statistical estimation procedure in the intention-to-treat population (ITT), which results in unbiased estimations under the missing-at-random assumption. The ITT analysis will be based on the available clinical data from all randomized families. The primary outcome analysis is the treatment group contrast (CHIMPs vs. TAU) at 18 months after baseline assessment in the ITT population of the children with an initial psychiatric diagnosis according to K-SADS-PL in a mixed logistic regression with the above-mentioned specification. The primary outcome is a psychiatric diagnosis according to K-SADS-PL (yes/no). Only the result of this comparison will be interpreted in a confirmatory manner. Additionally, this analysis will be repeated in the per protocol population. Sensitivity analyses will be performed for the primary outcome analysis with different methods of missing value imputation such as multiple imputation and last observation carried forward (LOCF) to study the robustness of the findings. Odds ratios, their 95% confidence intervals and *p*-values will be reported. The type I error will be set at 5% (two-sided). The secondary outcomes will be examined with appropriate methods in the ITT population in an exploratory manner. As far as possible, these outcomes will be operationalised as difference to baseline. Interim analyses are not planned. Subgroup analysis will be conducted on study sites, children's and adolescents' age and children's and adolescents' gender. A detailed statistical analysis plan will be finalized based on an analysis of a blinded, pooled data set. Statistical analyses will be carried out with SPSS, version 24 or newer (IBM Corp, Armonk, NY, USA) R, version 3.6.3 or newer (R Foundation for Statistical Computing, Vienna, Austria) or SAS, version 9.4 or newer (SAS Institute, Cary, NC, USA).

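### The sample size makes no allowance for loss to follow-up, so the stated 80% power for the 18-month primary contrast assumes nearly complete K-SADS-PL follow-up

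*Protocol article*

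**What the plan says.** The protocol article (Sample Size and Power Calculation) sizes the trial for hypothesis 4, in children with a K-SADS-PL diagnosis at baseline. It assumes that at 18 months "76% of children and adolescents in the intervention group and 90% in the control group still have a psychiatric diagnosis". The design parameters are "With a power of 80%, a two-sided alpha of 5% and an intracluster correlation of 0.05", and for family size "25/55/15/5% of the families have 1/2/3/4 children, so that on average a family has 2 children and adolescents".

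This gives 116 diagnosed children per group, 232 in total, in 116 families. The text continues: "We rounded up to 240 children and adolescents in 120 families". With 15% of children expected to have a baseline diagnosis, it concludes: "With this assumption, we have to recruit in total 800 families with 1,600 children and adolescents".

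For hypothesis 2, the same section expects 400 children with mental health problems at baseline and states 79% power for 80% versus 90%.

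Elsewhere the article anticipates loss:
- Study Centers makes loss to follow-up a topic of the steering committee and advisory board meetings.
- Data Assessment and Data Management (text after Figure 1) pays families for completed follow-ups, "in order to further promote a complete follow-up".
- Data Analysis relies on maximum likelihood under missing at random, with multiple imputation and LOCF as sensitivity analyses, and says: "The ITT analysis will be based on the available clinical data from all randomized families".

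No expected loss rate appears anywhere.

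**The concern.** The 240 children are counted at baseline, but the primary contrast is at 18 months. The power calculation treats the two counts as the same. Any diagnosed child without an 18-month K-SADS-PL reduces the number behind the 80% figure, and the plan keeps almost nothing in reserve.

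This matters because Data Analysis makes the hypothesis 4 contrast the only confirmatory result, and 80% is its stated power. A reader of a null result would take the type II error to be 20%. With moderate loss it would be larger, and nothing in the plan says so.

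**Working it through.** **Inputs (Sample Size and Power Calculation).** p1 = 0.76, p2 = 0.90, difference 0.14; two-sided alpha 0.05 (z = 1.960); power 80% (z = 0.8416); ICC 0.05; family sizes 1/2/3/4 in 25/55/15/5% (mean 2.0, SD 0.775, CV 0.387); planned 240 diagnosed children, i.e. 120 per group.

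**Step 1: reproduce 116 per group.** Two-proportion formula, unpooled variance:

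n = (1.960 + 0.8416)² × (0.76×0.24 + 0.90×0.10) / 0.14² = 109.1 per group.

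- Design effect for equal families: 1 + (2 − 1)×0.05 = 1.05. Then 109.1 × 1.05 = 114.5, which is 58 families of two, or 116 children.
- Design effect for unequal families: 1 + [(1 + 0.387²)×2 − 1]×0.05 = 1.065. Then 109.1 × 1.065 = 116.2.

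The stated figure reproduces. Clustering accounts for all of the increase over 109, so no attrition factor is hidden in it.

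**Step 2: follow the chain.** 232 is rounded to 240; 240/0.15 = 1,600 children; 1,600/2 = 800 families. Every step is exact. The margin is 240 − 232 = 8 children, and 8/240 = 3.3%.

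**Step 3: follow-up needed for 80% power.** Smallest whole number per group, out of 120:

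| Variance | Design effect | n per group | Share of 120 |
|---|---|---|---|
| Unpooled | 1.05 | 115 | 95.8% |
| Unpooled | 1.065 | 117 | 97.5% |
| Pooled | 1.05 | 118 | 98.3% |
| Pooled | 1.065 | 120 | 100% |

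The design effects of 1.05 and 1.065 assume about two diagnosed children per family. The plan introduces two as the average number of children per family, not of diagnosed children. If diagnoses were independent within families (an assumption), the share of families with at least one diagnosed child would be Σ w_k(1 − 0.85^k) = 0.272. That is about 218 of 800 families, with 240/218 ≈ 1.1 diagnosed children each. The average cluster size weighted by child is then about 1.2, and the design effect about 1 + 0.2×0.05 = 1.01. The follow-up needed drops to 109.1×1.01/120 = 91.8% (unpooled) or about 94% (pooled). If diagnoses aggregate in families, the truth lies between these cases.

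**Step 4: power at assumed loss rates.** Power = Φ(0.14 / √[(0.76×0.24 + 0.90×0.10)×DE/n] − 1.960), with n = 120 × (1 − loss); the pooled version uses the pooled standard error under the null. Each cell gives pooled–unpooled, in percent.

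| Assumed loss | n per group | DE 1.05 | DE 1.065 | DE 1.01 |
|---|---|---|---|---|
| 0% | 120 | 80.9–81.8 | 80.3–81.3 | 82.4–83.2 |
| 10% | 108 | 76.6–77.7 | 76.0–77.1 | 78.2–79.2 |
| 20% | 96 | 71.6–72.7 | 70.9–72.1 | 73.2–74.4 |
| 30% | 84 | 65.7–67.0 | 65.1–66.4 | 67.4–68.7 |

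**Step 5: detectable difference.** With 96 per group (20% loss), 90% in the control group, unpooled variance and design effect 1.05, the difference detectable with 80% power is 15.5 points rather than 14.

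**Step 6: hypothesis 2.** With 200 per group, 80% versus 90%, unpooled and design effect 1.05, power is 78.8%. This matches the stated 79%, but only if all 400 children have an 18-month outcome. Over both formulas at design effect 1.05, losses of 10/20/30% give about 74/69/63–64%.

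**The case against.** **The planned analysis is not a two-proportion test.** It is a mixed logistic model fitted by maximum likelihood to all available data, and K-SADS-PL is repeated at 6, 12 and 18 months. A child who misses only the last interview still contributes. This stands: the loss figures above give such a child no credit, so they are on the low side. The amount recovered cannot be computed from the document, and a child lost soon after baseline adds little to an 18-month contrast.

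**The calculation may contain unlabelled slack.** If diagnosed children average nearer one per family than two, the design effect is overstated. This also stands, and is why the required follow-up is given as a range. Even then the slack is used up at about 6–8% loss.

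**An article condenses the full protocol.** This does not help here. The article prints the whole derivation, and an allowance made elsewhere would give a target other than exactly 240/0.15.

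**The diagnosis rate may exceed 15%.** It may, but the plan states 15% as its expectation, not as a reserve, and the rate could equally be lower.

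**The consequences are limited.** The estimand, estimator and type I error are unaffected. Odds ratios with 95% confidence intervals will show the precision achieved. Hypothesis 2 is exploratory, and its 79% is already conditional on the 400 expected children. All of this stands and limits the severity.

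**Conclusion.** The point holds as an omitted planning assumption. The stated 80% power for the sole confirmatory contrast presupposes nearly complete 18-month follow-up: about 95–100% on the plan's own calculation, about 92–94% if diagnosed children cluster less than two per family. At an assumed 10% loss the shortfall against 80% is about 1 to 4 points; at 20%, about 6 to 9; at 30%, about 11 to 15. The loss rates are assumptions, and the power figures precede any recovery from the 6- and 12-month data.

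Three stronger readings are tempting, and the document does not support them:
- **A firm threshold of about 97% (232/240).** The break-even moves with the variance formula and the design effect, so only a range can be defended.
- **That 800 families cannot give 80% power at any realistic retention.** The plan gives no loss rate. Monitoring loss and planning missing-data analyses are routine and do not predict one.
- **That the sample size is miscalculated.** Every stated step reproduces; what is absent is an allowance for loss.

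This should be fixed. It concerns how the power claim is stated, not whether the test is valid.

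**What to change.** In the Sample Size and Power Calculation section, or in the SAP:

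1. State that 232 means children with a baseline diagnosis **and** an 18-month K-SADS-PL assessment, and that 240 is the number expected at baseline.
2. Report the power of the planned 800 families for hypothesis 4 at assumed losses of 0, 10, 20 and 30%, labelled as assumptions, with the detectable difference (about 15.5 points at 20% loss). Name the variance formula and the design effect used, and say whether two per family refers to all children or to diagnosed children.
3. Give the same range for hypothesis 2 (about 74/69/63% at 10/20/30% loss).
4. Note that these figures take no credit for the 6- and 12-month data in the mixed model.

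The cost is a few sentences and a less favourable power statement. Recruitment, design, endpoint and analysis model stay as they are.

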#### Outcome Measures

Sociodemographic information including age, gender, number of children, educational and employment status, somatic and psychiatric diseases, history of treatment and current treatment are recorded with a specifically designed questionnaire at baseline.

#### Primary Outcome Measure

Schedule for Affective Disorders and Schizophrenia for School Aged Children, Lifetime Version (K-SADS-PL).

The primary outcome in this study is the children's psychopathology measured by the German version of the K-SADS-PL (37, 38). The K-SADS-PL (Schedule for Affective Disorders and Schizophrenia for School Aged Children, Lifetime Version) is a standardized semi-structured interview for an early diagnosis of mental disorders in children and adolescents according to DSM-III-R and DSM-IV criteria. A trained external rater (blind to the family's group assignment) performs the K-SADS-PL by interviewing one parent for each participating child and adolescent—and in addition all children and adolescents aged 10 years and older about current and past episodes of the children's psychopathology. Children and adolescents are classified as having a psychiatric diagnosis if the interview of either the parent or the child or both indicate a psychiatric diagnosis. The K-SADS-PL has been widely used in research due to its good reliability and validity (39). The K-SADS-PL interviews are audiotaped for quality control.

#### Secondary Outcome Measures

##### Child Behavior Checklist/Youth Self Report

The children's psychopathology will further be assessed by the German version of the Child Behavior Checklist (CBCL) (40) and the Youth Self Report (YSR) (41). Both questionnaires describe a variety of internalizing and externalizing behaviors in children between the ages of 4 and 18. The CBCL consists of 113 items on which the parents are asked to rate the frequency of their children's behavior; a 3-point Likert-scale (0 = does not apply; 2 = clearly/often) is used. In addition, children 10 years of age and older report on their own behavior with the YSR. Children and adolescents are classified as having mental health problems, if the CBCL assessed by a parent or the YSR assessed by the child or both indicate mental health problems (T-score > 63). Both instruments provide raw and T-scores for internalizing and externalizing behavior as well as a total problem score. Due to their satisfactory psychometric properties (42), the CBCL and YSR are among the most widely used questionnaires in research.

##### KIDSCREEN-27

The health-related quality of life of the children is assessed by the KIDSCREEN-27 questionnaire (43). The KIDSCREEN instruments are a set of self-assessment questionnaires used to assess subjective health and well-being of children and adolescents between the ages of 8 and 18; corresponding versions for the parents' assessment of their children's quality of life are available. The short version of the KIDSCREEN questionnaire includes 27 items and covers 5 health-related quality of life dimensions. The questionnaire assesses the child's quality of life in consideration of his or her physical, mental and social well-being. Health-related quality of life is assessed by one parent for each participating child and adolescent and in addition by all children and adolescents aged 10 years and older. A short version of the KIDSCREEN 27 questionnaire, the KIDSCREEN 10 questionnaire, will be used for the calculation of QALYs for children and adolescents (44, 45).

##### Children Global Assessment Scale

In addition, the children's global impairment will be assessed by the German Skala zur Gesamtbeurteilung von Kindern und Jugendlichen (SGKJ) (46), the German version of the Children Global Assessment Scale (CGAS) (47). This scale is the internationally most commonly used scale for the assessment of the severity of psychiatric disorders in children and adolescents. The severity of the disorder is rated on a scale from 1 (needs constant supervision) to 100 (superior functioning in all areas).

##### Brief Symptom Inventory and Patient Health Questionnaire

The parent's symptomatology will be assessed by the German version of the Brief Symptom Inventory (BSI) (48), a short version of the Symptom Checklist-90-Revised (SCL-90-R). This self-assessment questionnaire measures psychological symptoms during the last 7 days. Parents are asked to rate their individual psychological stress on a 5-point Likert-scale from 0 (“not at all”) to 4 (“very strong”). In addition to the BSI, the German version of the Patient Health Questionnaire (PHQ-D) (49) is applied to screen for depressive, anxiety, somatoform, alcohol, and eating disorders. The PHQ-D showed good agreement with the Structured Clinical Interview for DSM-IV (SCID-I) (49); good validity of the PHQ-D for the diagnostic of psychiatric disorders can therefore be assumed. Further aspects of the parental psychopathology will be assessed by the German versions of the Clinical Global Impressions Scale (CGI) (50) and of the Global Assessment of Functioning (GAF) (51). While the CGI is used to measure the severity of the disease, the GAF is used to rate the person's overall level of functioning.

##### European Quality of Life 5 Dimensions Scale

The parents' health-related quality of life is assessed by the German version of the European Quality of Life 5 Dimensions Scale (EQ-5D) (52–54). This health questionnaire expresses the patient's quality of life. The EQ-5D defines the participants' health states at 5 dimensions (mobility; ability to fend for oneself; daily activities; pain; anxiety); The EQ-5D is the most frequently used instrument worldwide for the assessment of health-related quality of life in adults and will be used for the health-economic analyses.

##### Freiburg Questionnaire of Coping With Illness (Freiburger Fragebogen zur Krankheitsverarbeitung)

The Freiburg Questionnaire of Coping with Illness (Freiburger Fragebogen zur Krankheitsverarbeitung, FKV) (55) is a self-report instrument that assesses the parents' coping with the disorder. The FKV assesses a broad spectrum of coping mechanisms on the levels of cognition, emotion and behavior. The short version includes 35 items on the 5-point Likert-scale from 1 (not at all) to 5 (very strong) and is particularly appropriate for follow-up measurements.

##### General Family Questionnaire (Allgemeiner Familienfragebogen)

Family relations and family functioning will be assessed by the German General Family Questionnaire (Allgemeiner Familienfragebogen, FB-A) (56). This self-report instrument focusses on the family system and includes the scales task fulfillment, role behavior, communication, emotionality, affective establishment of relationships, control, values and norms, social desirability, and defense. Forty items are answered on a 4-point Likert-scale ranging from “exact agreement” to “no agreement at all.”

##### Global Assessment of Relational Functioning Scale

In Addition, the dysfunction and relational health of the family is rated based on the German version of the Global Assessment of Relational Functioning Scale (GARF) (51).

##### Oslo Social Support Questionnaire

The Oslo Social Support Questionnaire (OSSQ) (57) measures social support of parents and children. The original version of the OSSQ consists of three items regarding (1) the number of confidants, (2) the sense of interest from other people and (3) the relationship to neighbors. An extended version developed by our research group was used, covering prospective individuals providing social support.

##### Questionnaire for the Assessment of Therapy Outcome (Fragebogen zur Beurteilung der Behandlung)

The evaluation of the treatment will be assessed by the Questionnaire for the Assessment of Therapy Outcome (Fragebogen zur Beurteilung der Behandlung, FBB) (58), which offers the possibility to assess the subjective quality of care according to the two main aspects quality of results (treatment success) and process quality (treatment procedure).

##### Comparative Psychotherapy Process Scales (Vergleichende Psychotherapie Prozess Skalen)

The therapeutic process is also assessed by the Comparative Psychotherapy Process Scales (Vergleichende Psychotherapie Prozess Skalen, VPPS) as the German translation of the Comparative Psychotherapy Process Scale (CPPS) (59, 60). The VPPS was developed to measure therapeutic activity like the process and techniques that are used in the therapeutic setting. It was designed as a primarily descriptive measure (i.e., what was done), but not as an evaluative measure (i.e., how it was done). The aim of the VPPS is to describe the therapeutic session as accurately and objectively as possible.

